### Measurements

Screening for inclusion and exclusion criteria will occur at the laboratory setting and will be performed by the primary investigator ([name]) of this study. All subjects will sign an informed consent form in accordance with the University of Groningen Medical Ethics Committee prior to participation.

Lower extremity kinematic, kinetic and EMG data of subjects performing a sidestep-cutting manoeuvre in the laboratory will be analysed. The primary outcome measurements will be as follows:

1) Knee abduction moment

2) Loading rate of knee abduction moment over time

Secondary outcome parameters will be as follows:

3) Average EMG pattern of the gluteus maximus (GM), vastus medialis (VM), vastus

lateralis (VL), medial hamstring (MH), lateral hamstring (LH), medial gastrocnemius

(MG) and lateral gastrocnemius (LG)

4) Muscle onset time (ie. the first burst in EMG as detected by the Santello algoritm prior

to landing [66]) of the GM, VM, VL, MH, LH, MG and LG

5) Muscle activity of the GM, VM, VL, MH, LH, MG and LG integrated over the interval from 100 milliseconds prior to foot contact to foot contact (preparatory interval) and from foot contact to the point of peak knee flexion (weight acceptance)

6) Muscle co-contraction (ie. using the integrated EMG of each muscle and the formula: [(less active muscle/more active muscle) X (sum of the integrated activity of both muscles)]) of VL-MG, VL-LH, VM-LG and VM-MH over the interval from 100 milliseconds prior to foot contact to foot contact (preparatory interval) and from foot contact to the point of peak knee flexion (weight acceptance)

7) Hip, knee and ankle angles at IC, peak posterior GRF and the maximum values for each of those variables

a. Abduction/adduction

b. Flexion/extension

c. External/internal rotation (only for hip and knee)

8) Knee angular displacement flexion angle

9) Joint moments of hip, knee and ankle at IC, peak posterior GRF and the maximum values for each of those variables

a. Abduction/adduction (not for knee, see primary outcome measurement)

b. Flexion/extension

c. External/internal rotation (only for hip and knee)

In addition we will record the history on injuries and/or surgeries, the Tegner activity level questionnaire [69,70] and activity between intervention and follow up tests.

### Subject preparation

In order to calculate the hip, knee and ankle joint angles and moments, anthropometric measurements will first be taken in preparation of the 3D motion analysis testing. Anthropometric measurements will include body weight and height, knee and ankle diameter and leg length (ASIS - medial malleolus). Subjects will then have reflective markers placed over the heel, lateral malleolus, second metatarsal head, femoral epicondyle and ASIS and PSIS bilateral. Another four markers will be placed bilaterally on the lateral side of the mid-thigh and mid-calf. EMG signals will be recorded using silver-silver chloride, pre-gelled bipolar surface electrodes (ZeroWire EMG, Aurion, Italy). Electrode locations will be located via palpation of the subject's anatomy and will be placed over the appropriate muscle belly in line with the direction of the fibres with an interelectrode distance of approximately 20 mm, which is in accordance with the work of Delagi and Perotto [71]. Electrode sites will be shaved, abraded and cleaned with isopropyl alcohol to reduce impedance. The electrodes will be secured to the subject's skin with tape to minimise motion artefact. Electrode placement will be confirmed through visual inspection of signals on the computer screen using Vicon Nexus Software (Version 1.6, Vicon Motion Systems, Inc., Centennial, CO) during standardised manual muscle testing [29]. Two seconds of maximal voluntary isometric contraction (MVIC) EMG signals will be collected from each muscle before data collection. These data will be processed and used for normalisation of the corresponding muscle's EMG activity during the dynamic task. The same investigator ([name]) will perform all electrode and marker placements. All the subjects will wear tight-fitting shorts and their own indoor basketball shoes.

An unanticipated cutting task will be carried out in the laboratory. Each athlete will complete a practice session that includes several anticipated and unanticipated trials of each of the two tasks to familiarise his-/herself with the experimental setup as well as to reduce the effect of targeting the force platform. The athlete will randomly perform cutting trials. The straight run and cross-step are catch tasks so as to present the athletes with three options. Consequently, the cutting manoeuvre becomes an unanticipated task. Specifically, the cutting manoeuvre consists of an approach run, followed by a plant-and-cut manoeuvre at a 45° angle with the dominant foot on the force platform. The cutting direction will be to the right for left-footed subjects and to the left for right-footed subjects. Each angle will be measured from the centre of the force plate and the corresponding line will be marked (using tape) so that it can be clearly seen by the subjects. As for the straight ahead run, the subjects continue the approach run through the experimental setup, with a change in neither direction nor speed.

Two infrared timing gates will be used to ensure that the approach speed will be 4.5-5.5 m/s and 0.5 seconds before the subjects land on the force platform and make the cut, a 3-light guiding system will be used to randomly cue the subjects; one light will turn on, indicating the direction the subject should go. Each subject will be given 1 minute between trials to reduce the potential effects of fatigue. To make sure there is pressure on the performance, the exit speeds needs to be 4.0-5.0 m/s, measured by the infrared timing gaits, 5 meters beyond the force plat form.

Only successful trials will be kept. A cutting trial is deemed successful if the subjects approaches the force platform with the required speed, performs the manoeuvre with the target board illuminating a light, makes IC with the force platform and either runs straight ahead or changes direction at a 45° cut angle with the required exit speed. Subjects will be required to continue running after sidestep execution for 5 meters. Cutting trials during which the subject modifies his/her stride length (i.e., stutter-step) to make contact with the force platform will also be discarded. The stutter-step will be discarded as these trial will not be comparable with the other trials; the speed will in all likelihood decrease and will not be between 4.5-5.5 m/s anymore. Approach speed is based on previous studies [69,72].

### Instrumentation

Vicon's Nexus software (Version 1.6) of the Vicon Motion Analysis System (Vicon Motion Systems, Inc., Centennial, CO) will be used to collect and calculate the kinematic and kinetic data. GRF data will be collected at 1200 Hz by 2 force plates (Bertec Corporation, Columbus, Ohio) that are located within a custom-built flooring system in which the force plates are flush with the surrounding surface. Surface electromyographic (EMG) signals will be collected with the Noraxon Telemyo Telemetry EMG System (Noraxon USA Inc, Scottsdale, AZ) using ZeroWire. Signals will be passed from the electrodes to the transmission unit. After amplification, the telemetry signals will then be passed from the transmitter to the receiver for further amplification (overall gain of 2000) and filtered with a bandwidth filter (10 Hz low pass 500 Hz high pass Butterworth filter, common mode rejection ratio of 130 db). Signals from receiver will be collected with the data acquisition package Vicon Nexus Software (Version 1.6, Vicon Motion Systems, Inc., Centennial, CO). The analog signal from the EMG receiver will be converted to a digital signal via a DT3010/32 (32 channel, 24 bit) A/D board (Data Translation, Inc., Marlboro, MA). Basler camera's (640 × 480, 210 fps, Vicon Motion Systems, Inc., Centennial, CO) with a 25 mm C-mount lens will be used to collect analog high-speed data.

### Data acquisition and statistical analysis

Hip, knee and ankle joint kinematics will be evaluated at IC, peak posterior GRF and the maximum values for each of those variables. IC will be defined as the point in time when 5% of the subject's body weight is upon the force plate. The raw coordinate data will be filtered using an optimised cut off frequency.

Raw analog data from the MVICs and synchronised raw analog data (joint kinematic, joint kinetic data and GRF data) from the jump trials will be imported into Matlab (release 12, The MathWorks, Natick, MA) for data processing and identification of the variables of interest. The mean value of each MVIC will be used for normalisation of the EMG during the jump trials. Both the MVIC and trial EMG data will be processed with a linear envelope before filtering by a Butterworth filter (fourth-order, zero-phase shift, cut off frequency of 20 Hz).

Raw analog data from the force plates will be used to calculate the GRF data for each jump trial. The raw coordinate data will be filtered using an optimised cut off frequency. The GRF will be filtered using a fourth-order Butterworth filter at a cut off frequency of 100 Hz. The GRF data will be used to calculate the maximum posterior GRF during the initial-stance phase of the jump tasks.

Only the dominant leg will be analysed. In addition to the 30 trials during the intervention and retention tests, all subjects will perform five trials to begin with. These five baseline trials (without feedback) prior to the intervention will be conducted to assure homogeneity across groups on the primary outcome measures (knee abduction moment and the loading rate of knee abduction moment over time). The results of these five trials will be compared to each other using a one-way ANOVA. Multilevel analysis will be applied to examine the within and between subject effects. The learning curve with implicit versus explicit versus no feedback of the primary outcome measures over time will be analysed using SPSS 18.0 (SPSS Inc., Chicago, IL). The secondary outcome measurements will be used as explanatory variables. In addition, post-hoc Bonferroni adjustments will be conducted for the within, between and interaction effects. An alpha level of 0.05 will be set a priori.

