## Methods/Design

### Study design

This will be a randomised controlled laboratory study with two between-subject factors (gender and intervention group (ie. implicit, explicit and control group)) and one within-subject factor (time, ie. pretest, one week posttest and one month posttest). After consent to participate, subjects will be randomly assigned to a group based on the order in which they sign up for the initial baseline testing session. As an equal number of males and females per group (2 × intervention group and 1 × control group) is essential, stratified sampling will be carried out. The study design, procedures and informed consent are approved by the local Medical Ethical Committee (registration number 2009-142).

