We take the knee abduction moment and the loading rate of knee abduction moment over time as the main variables of interest as the main training purpose of this study is to get alignment of the leg in line with the GRF. When taking the clinical relevance of an 'at risk' and a 'not at risk' abduction moment into account, we refer to the prospective study by Hewett et al. [61]. The females in that study who ruptured their ACL (n = 9) had a greater stance phase peak external knee abduction moment, -45.3 ± 28.5 Nm, compared to that of uninjured females (n = 390), -18.4 ± 15.6 Nm (P < 0.001). We considered this mean difference in knee abduction moment to be clinically relevant, as it was predictive of ACL injury occurrence in a prospective study. We therefore used the difference to calculate the power for this study. With an effect size of 0.55 (determined based on those differences of the means divided by the pooled SD) and an alpha of 0.05, we reach a power of 0.80 when including 120 subjects, which means 40 subjects (20 females and 20 males) per group (ie. implicit learning group, explicit learning group and control group). G*Power for Mac, Version 3.1.2 has been used to calculate the needed sample size.

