The best performance so far will be based on the peak valgus moment, which needs to be as low as possible. The total training session consists of 30 trials. As we need to make sure that the improvements in landing performance (if any) are permanent rather than temporary, a retention test will be conducted one week (similar to Onate et al.) [70] and one month later. During the retention tests no feedback at all will be given to either group. The control group will perform the exact same tasks as the intervention groups. The control group, however, will not receive any feedback during any trial. To make sure three homogeneous groups are participating, five trials with no feedback will be performed prior to the real intervention (ie. in addition to the 30 trials).

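### The pretest level of time matches no session in Table 1, and the five no-feedback trials have only a homogeneity test as stated use; they should be defined as the baseline and adjusted for

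*Protocol article*

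**What the plan says.** Under Study design, the article specifies gender and intervention group as between-subject factors and "one within-subject factor (time, ie. pretest, one week posttest and one month posttest".

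Table 1, under Intervention, has three rows: T1 (intervention), T2 (retention at one week) and T3 (retention at one month). At T1 the explicit and implicit groups perform 30 trials with feedback and the control group performs 30 without. No row is a pretest.

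The text under Intervention adds untreated trials: "To make sure three homogeneous groups are participating, five trials with no feedback will be performed prior to the real intervention". The section Data acquisition and statistical analysis repeats that purpose for both primary outcomes and gives the method: "The results of these five trials will be compared to each other using a one-way ANOVA". It then announces a multilevel analysis, names the secondary outcomes as explanatory variables, and lists within, between and interaction effects. It does not say which data form the pretest level, and it gives the five trials no role in that model.

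**The concern.** Two things are fixed badly.

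- **The test cannot do the job given to it.** A non-significant ANOVA does not show that the arms are alike, and it does not remove whatever imbalance is present. The imbalance carries into the follow-up comparison in proportion to the correlation between baseline and follow-up.
- **The pretest is not tied to a session.** Study design and Table 1 do not line up. An analyst could take the five trials as the pretest, leave them out of the model, or take T1 as the first time point. These choices estimate different things with different precision. T1 is already treated in two arms, so a contrast taken from T1 would subtract part of the effect under study.

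The baseline value of the primary outcome is likely to be a strong predictor of its retention value, and it is already being collected. How it enters the model affects both precision and protection against chance imbalance.

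**Working it through.** **Inputs.** From Study population: effect size 0.55, alpha 0.05, power 0.80, 120 subjects, 40 per arm. From Study design: three time levels. The correlation r between baseline and follow-up is not in the article; I assume 0.5 to 0.7. I take 0.55 as a standardised difference d, as given. It does not follow from the quoted means and SDs (26.9/15.96 = 1.69 with the n-weighted pooled SD), but that is a separate matter.

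**1. The plan's own figure.** The article says "we reach a power of 0.80 when including 120 subjects" without naming the test. A repeated-measures between-factors F test reproduces it with f = 0.55/2 = 0.275, six cells (3 arms × 2 sexes), m = 3 measurements and correlation 0.5:

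λ = f²·N·m / (1 + (m − 1)r) = 0.0756 × 120 × 3 / 2 = 13.6, power 0.805 (minimum N = 119).

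A one-sided comparison of two arms of 40 also comes close (0.79). A two-sided comparison of two arms, the standard used below, has power 0.68 (exact t).

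**2. What the baseline test can show.** The standard error of a difference between two arm means is √(2/40) = 0.224 SD.

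- Imbalance of 0.3 SD: z = 0.3/0.224 = 1.34, two-sided p = 0.18. So 0.3 SD or more arises by chance in about 18% of trials for a given pair of arms.
- A pairwise test at 5% passes anything below 1.96 × 0.224 = 0.44 SD.
- Three-arm ANOVA with two arms 0.3 SD apart and the third midway: F = 40 × (0.15² + 0.15²)/2 = 0.9 on 2 and 117 df, p = 0.41. With the third arm level with one of the two: F = 40 × (0.1² + 0.1² + 0.2²)/2 = 1.2, p = 0.30.
- What a 0.3 SD imbalance leaves in an unadjusted follow-up comparison: r × 0.3 = 0.15 to 0.21 SD, against a design effect of 0.55. A change score overcorrects by (1 − r) × 0.3 = 0.15 to 0.09 SD. Covariate adjustment removes the imbalance on average.

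**3. Power under each use of the five trials** (40 against 40, d = 0.55, two-sided, single follow-up). Effective d is 0.55 without baseline, 0.55/√(2(1 − r)) for change, and 0.55/√(1 − r²) with the covariate.

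| r | Baseline left out | Change (group-by-time) | Covariate |
|---|---|---|---|
| 0.5 | 0.68 | d = 0.550, 0.68 | d = 0.635, 0.80 |
| 0.6 | 0.68 | d = 0.615, 0.78 | d = 0.688, 0.86 |
| 0.7 | 0.68 | d = 0.710, 0.88 | d = 0.770, 0.93 |

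**4. A group main effect over three levels.** With an untreated pretest among them, the averaged effect is 0.55 × 2/3 = 0.367. Its variance is (1 + 2r)/3, so effective d is 0.449 at r = 0.5 and 0.410 at r = 0.7, with power 0.51 and 0.44. This applies only if that averaged effect is interpreted.

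**The case against.** The strongest reply is that the five trials are the only untreated data, so the natural reading makes them the pretest level, already inside the multilevel model. A group-by-time contrast then uses baseline, and nothing is diluted. That stands, and it is why the change contrast is the fair comparator. The gain is 0.68 to 0.80 at r = 0.5 and 0.88 to 0.93 at r = 0.7, not 0.68 to 0.93.

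Averaging T2 and T3 also helps without any baseline. With r = 0.5 throughout, the variance is (1 + 0.5)/2 = 0.75 and power is 0.80. The covariate still adds: variance 0.75 − 0.25 = 0.50, effective d = 0.778, power 0.93.

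It is also fair that an article may leave covariates and the coding of time to a fuller document. That answers a complaint about a missing covariate. It does not answer a stated method unfit for its stated purpose, or a time level that Table 1 does not contain. Assignment linked to sign-up order gives some reason to look at baseline, but a descriptive table serves that purpose.

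A reader might infer more than the text supports:

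- *That the baseline trials are excluded from the model.* No section says so; the ANOVA is merely their only stated use.
- *That the treatment effect is diluted.* The article frames the question as learning curves over time and lists interaction effects. Between effects are listed too, but none is made decisive.
- *That lost precision and dilution add up.* The first needs the five trials outside the model, the second a pretest inside it.
- *That the ANOVA result decides something.* No decision is attached to it.
- *That the ANOVA inflates type I error by treating repeated trials as independent.* The unit of analysis is not stated; one mean per person is equally open.

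**Conclusion.** The point holds in limited form. Study design and Table 1 disagree on the first time level and must be reconciled, and the homogeneity test cannot deliver what is claimed for it: an imbalance of 0.3 SD passes easily and is not corrected by passing.

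Adjusting for the five-trial mean is a better use of data already planned. Against a change contrast from the same trials, the gain in power is about 0.12 at r = 0.5 and 0.05 at r = 0.7. Against leaving baseline out, it is 0.12 to 0.25. These figures rest on the assumed correlation, on d = 0.55 taken as given, and on a two-sided comparison of two arms at one follow-up. The two-thirds dilution is conditional on interpreting a group main effect averaged over an untreated pretest. This is a worthwhile improvement and clarification; it does not show that the planned analysis is invalid.

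**What to change.** - State that the pretest is each person's mean over the five no-feedback trials, and add it to Table 1 as a separate row before T1.
- Fit the multilevel model with T2 and T3 as outcomes and terms for arm, gender, session and arm-by-session. Include the pretest mean as a covariate, or use a constrained-baseline model, whatever imbalance is observed.
- Analyse the T1 feedback trials separately as the acquisition curve, and do not use them as the pretest.
- Read the treatment effect from the post-intervention sessions or the group-by-time contrast, not from a main effect that averages in the pretest.
- Replace the one-way ANOVA with a descriptive baseline table by arm and gender.

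The cost is analysis wording and one table row. No extra trials, visits or subjects are needed.

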## Abstract

**Background:**

Of all athletic knee injuries an anterior cruciate ligament (ACL) rupture results in the longest time loss from sport. Regardless of the therapy chosen, conservative or reconstructive, athletes are often forced to reduce their level of physical activity and their involvement in sport. Moreover, a recent review reported prevalences of osteoarthritis ranging from 0% to 13% for patients with isolated ACL-deficient (ACL-D) knees and respectively 21% to 48% in patients with combined injuries. The need for ACL injury prevention is clear. The identification of risk factors and the development of prevention strategies may therefore have widespread health and economic implications. The focus of this investigation is to assess the role of implicit and explicit motor learning in optimising the performance of a side-step-cutting task.

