**Discussion:**

Female athletes have a significantly higher risk of sustaining an ACL injury than male athletes. Poor biomechanical and neuromuscular control of the lower limb is suggested to be a primary risk factor of an ACL injury mechanism in females. This randomized controlled trial has been designed to investigate whether individual feedback on task performance appears to be an effective intervention method. Results and principles found in this study will be applied to future ACL injury prevention programs, which should maybe more focus on individual injury predisposition.

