When observers see a motor event that shares features with a similar motor event present in their motor repertoire, they are primed to repeat it. The greater the similarity between the observed event and the motor event, the stronger the priming is [54]. The activation of motor representations through mere observation could have important applications in enhancing skill learning and in motor rehabilitation [55]. We therefore want to apply an intervention in which the subjects see their own performance, implicitly or explicitly. Priming will be strong, as seeing one's own performance will result in great similarity between the observed event and the executed event.

The goal of this research project is to investigate how we can train athletes individually to use certain motor patterns, that eventually become automatic. Motor learning that is offered in an implicit manner, will potentially be more robust once on the field. Our research project might give more insight in the ongoing problem of ACL injuries and might give the opportunity to more effectively implement prevention programs targeted towards the individual needs. If individual visual implicit feedback on task performance appears to be an effective intervention method, this could be applied to larger populations participating in team sports with a high risk of sustaining an ACL injury. Results and principles found in this study will be applied to future ACL injury prevention programs.

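### Post-hoc Bonferroni over an undefined family costs the three arm comparisons power that Shaffer's step-down would partly recover with the familywise error still held at 0.05

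*Protocol article*

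**What the plan says.** The Study design section describes "two between-subject factors (gender and intervention group (ie. implicit, explicit and control group)) and one within-subject factor", the last being time (pretest, one week, one month). The section on data acquisition and statistical analysis fits a multilevel model and states: "The learning curve with implicit versus explicit versus no feedback of the primary outcome measures over time will be analysed using SPSS 18.0". Its multiplicity rule is one sentence, "post-hoc Bonferroni adjustments will be conducted for the within, between and interaction effects", followed by "An alpha level of 0.05 will be set a priori". It gives no number of tests over which alpha is divided, and it does not separate the arm pairs from the gender and time effects.

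The Study population section sizes the trial at 40 per arm for an effect of 0.55, with "an alpha of 0.05, we reach a power of 0.80 when including 120 subjects". No division of alpha is mentioned there.

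The condition for success is worded in more than one way. The Abstract's Discussion paragraph says the trial is to "investigate whether individual feedback on task performance appears to be an effective intervention method". The end of the Background says: "If individual visual implicit feedback on task performance appears to be an effective intervention method, this could be applied to larger populations". The main Discussion repeats that sentence for visual feedback, with the word implicit left out. The Abstract's Background paragraph gives the focus as to "assess the role of implicit and explicit motor learning in optimising the performance of a side-step-cutting task".

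**The concern.** The trial's question lies in three comparisons: implicit against control, explicit against control, and implicit against explicit. The stated rule treats them as part of one undifferentiated set of within, between and interaction effects. Two things follow.

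- **The penalty is unknown.** Alpha may be divided by three, by the number of factorial effects, or by something else, and this can be settled after the data are seen.
- **The penalty is larger than it has to be.** Even on the mildest reading (three pairs), plain Bonferroni ignores the logical links between the three hypotheses. A sharper procedure with the same error guarantee exists.

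At stake is the chance of confirming a real feedback effect in a trial whose sample size was justified at an undivided 0.05. The shifting success wording adds to this. A reader cannot tell whether a positive result means that feedback works or that implicit feedback works, and the rationale for implicit over explicit learning invites a third claim.

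**Working it through.** **Inputs.** 40 per arm, effect d = 0.55, alpha 0.05 and power 0.80 come from the Study population section. Neither sidedness nor family size is stated; two-sided tests and the family sizes below are assumptions. All figures are for one outcome at one time point, with SD 1.

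**1. The protocol's own figure.** For two arms of n each, power is approximately Φ(d√(n/2) − z), and d√(n/2) = 0.55 × √20 = 2.460.
- One-sided 0.05: Φ(2.460 − 1.645) = 0.79. This reproduces the stated 0.80, as one undivided two-arm comparison.
- Two-sided 0.05: Φ(2.460 − 1.960) = 0.69.

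**2. Cost of Bonferroni for one arm pair** (noncentral t, 78 df, two-sided):

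| Level | Assumed family | Power |
|---|---|---|
| 0.05 | none | 0.68 |
| 0.05/3 | three arm pairs | 0.51 |
| 0.05/6 | three pairs × two primary outcomes | 0.41 |
| 0.05/7 | seven effects of gender × group × time | 0.39 |

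For 80% power by the same t calculation, 53 per arm are needed at 0.05 and 71 at 0.05/3. Leaving the pairs unadjusted is not the answer: by simulation, three pairs at 0.05 each give a familywise error of 0.12.

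**3. Why Shaffer's step-down is valid and never worse.** Order the three p-values. Test the smallest at 0.05/3; if it is significant, test the other two at 0.05.
- *Never worse.* If the smallest p-value misses 0.05/3, neither method rejects anything. If it passes, the other two face 0.05 instead of 0.05/3. Every Bonferroni rejection is therefore kept.
- *Error, all three arms equal.* A false rejection needs the smallest p-value to pass 0.05/3, so the probability is at most 3 × 0.05/3 = 0.05. The simulated value is 0.043, the same as for Bonferroni.
- *Error, exactly one pair equal.* Only one hypothesis is true, and it is never tested above 0.05.
- *Exactly two pairs equal* cannot occur, because the third would then be equal too.

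**4. Power gained** (simulated three-arm trials, 40 per arm, pooled variance, 117 df; means in the order implicit, explicit, control):
- (0.55, 0.55, 0): implicit against control is significant in 0.51 of trials under Bonferroni and 0.59 under Shaffer.
- (0.55, 0, 0): implicit against explicit is significant in 0.51 to 0.52 under Bonferroni and 0.59 under Shaffer.
- (0.55, 0.275, 0): the gain is smaller. In a rerun of this simulation, implicit against control rises from 0.51 to 0.54.

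**The case against.** **Bonferroni is valid.** An overall test followed by Bonferroni-adjusted pairs is a recognised procedure. This stands: the plan does not inflate error on that reading, and the point concerns lost power and an undefined family.

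**The size rests on assumptions.** The protocol states no family size. The multilevel model uses baseline and repeated trials, which the simple calculation ignores. The value 0.55 also does not follow from the means and SDs quoted beside it: 45.3 − 18.4 = 26.9 Nm, which gives 1.17 with the root-mean-square SD and 1.69 with the n-weighted pooled SD. At effects that large, pairwise power exceeds 0.99 even at 0.05/7, and the choice of procedure hardly matters. All of this stands as a limit on the magnitude, but not on the ordering, since Shaffer's method is never worse.

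**Detail of this kind may sit in a full analysis plan.** True of naming a primary contrast, so its absence alone is not pressed here. The article does, however, fix Bonferroni and its scope, and that stated choice can be improved.

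**A stronger reading a reader might infer** is that the same data can support opposite answers. If both feedback types work equally (0.55 SD), implicit beats control without beating explicit in about 66% of trials unadjusted and 51% under Bonferroni. In that scenario both findings are true: they are correct answers to two different questions. The planned Bonferroni pairs would, on the ordinary reading, include implicit against explicit, so a claim of superiority would contradict the trial's own test. The Background sentence about wider use is also a remark on what could follow, and not a decision rule.

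**Conclusion.** The point holds as one about efficiency and definition. The Bonferroni family is not defined and, even on the mildest reading, the three arm comparisons lose power needlessly: 0.51 per pair against 0.68 unadjusted, of which Shaffer's step-down recovers up to about 0.59 with familywise error across the pairs still at or below 0.05. This assumes 40 per arm, d = 0.55, one outcome, one time point, two-sided tests and a family of three pairs. A wider family would make the loss larger; a larger true effect would make it smaller. The success wording in the Abstract, Background and main Discussion is inconsistent and needs one meaning. The documents do not support saying that the plan yields contradictory conclusions.

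**What to change.** In the section on data acquisition and statistical analysis:

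1. For the three arm pairs within each primary analysis, replace Bonferroni with Shaffer's step-down: smallest p-value at 0.05/3; if significant, the other two at 0.05.
2. Keep gender and time main effects and gender interactions outside this family, labelled exploratory and reported as estimates with confidence intervals.
3. State that implicit feedback will be called better than explicit only if the implicit-against-explicit contrast is significant.
4. Reconcile the success wording in the Abstract's Discussion paragraph, the end of the Background and the main Discussion.

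A fixed testing order (implicit against control, then implicit against explicit, then explicit against control) is not recommended. When both feedback types work equally, it would confirm explicit against control in only 1.2% of trials, against 51% under Bonferroni.

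The cost is a few sentences, with no new subjects or data; the procedure can be applied by hand to three unadjusted p-values. It loses no rejections relative to three-pair Bonferroni. It does not come with simple matching simultaneous confidence intervals, so the intervals reported should be labelled accordingly. The change does not settle multiplicity across the two primary outcomes and the two retention tests, which needs its own rule.
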